#### Large-Scale Trial Feasibility

To determine the feasibility of a full-scale trial, we will look at response rates, ease of implementation, and outcome appropriateness, as well as learn how participants respond to the instruments. The response rate on the surveys will serve as a proxy of instrument feasibility and will be calculated as the number of items answered on a survey divided by the total number of survey questions. A “does not apply” answer will count as an item nonresponse, or unanswered. If a 75% response rate or higher is achieved, then the instrument will be deemed feasible. A list of the questions that were answered versus unanswered will also be compiled to improve the instruments.

Ease of implementation, on the other hand, will be measured solely in the key informant interviews. Staff will be asked open-ended questions on their experiences with participant recruitment and use of the tool, for example, “What were some facilitators or challenges to recruiting participants?” “...to the use of the tool in your meetings?”

Perceived outcome appropriateness, finally, will be measured qualitatively through questions on the SC+ follow-up survey and informant interviews on whether housing knowledge, self-efficacy, and staff trust were appropriate to measure for the tool, as well as whether participants recommended other outcomes to measure.

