### Research Questions

Through this study protocol, we are seeking to answer the following research questions: (1) What is the initial treatment effect of SC+ (standard care plus), as compared to SC (standard care), on survivors’ housing knowledge, housing self-efficacy, and staff trust? (2) What is the estimated sample size needed for a full-scale intervention trial? What is the estimated timeline needed to reach this sample size? (3) Are the expected rates of recruitment and retention achieved? (4) Are the study’s processes and instruments feasible for a full-scale intervention trial? and (5) Is the tool acceptable and usable by survivors and staff?

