#### Sociodemographics

The study will collect sociodemographic information from participants at baseline. Variables include age, gender, income, length of time with the site, prior or current domestic violence exposure, housing status, and experiences of housing instability in the last 6 months.

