#### Housing Knowledge

As no known prior studies have measured housing knowledge, we will assess whether the tool improves survivors’ knowledge of housing options through a 10-item Housing Knowledge Quiz developed for this study (Table 2). Questions like “Which housing program is a lottery of affordable housing apartments in New York City?” will ask survivors about affordable housing programs in New York City and program eligibility criteria, with each question carrying a 1-point weight for a possible summed score range of 0 to 10.

**Table 2 table2:** Housing knowledge quiz.

Question	Answer choices
1. Jane is a survivor of domestic violence in shelter. She and her two children plan to move out of shelter to an apartment. What is Jane’s household size?	1,2,3
2. “Affordable housing” means that you pay about one-third or less of your income on rent.	True, False
3. Eligibility for New York City housing programs can depend on your...	Household size, Income amount, Citizenship or residency status, Current living situation, Whether you have children or are expecting children, Disability, All of the above
4. Which housing program is a lottery of affordable housing apartments in New York City?	FHEPS^a^, Housing Connect, Property Management Companies, Do Not Know. Please select one answer.
5. Which housing program lists apartment openings, reviews housing applications, and takes payment?	FHEPS, Housing Connect, Property Management Companies, Do Not Know. Please select one answer.
6. Which housing program is a type of rental assistance paid directly by the government to the landlord? The amount of rental assistance will vary by one’s income and household size.	FHEPS, Housing Connect, Property Management Companies, Do Not Know. Please select one answer.
7. DHS^b^ shelter provides a time-limited stay only for households of domestic violence.	True, False
8. Supportive housing is a type of permanent housing that also includes services like case management, medical, and psychiatric help.	True, False
9. Who may be eligible for SSI^c^ benefits?	Individuals or couples who are 65 years or older, blind, or disabled, with limited income and resources, Children who are disabled or blind, with limited income and resources, All of the above, None of the above
10. What is the name of a property management company that manages affordable and low-income housing in New York City?	Reliant Realty, Insignia, Barrier Free Living, Urban Resource Institute. Please select one answer.

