#### Housing Self-Efficacy

According to social cognitive theory, the stronger one’s self-efficacy, the higher the goals one sets and the more favorable the outcomes one expects, and vice versa [33]. In Cattaneo and Chapman’s [28] empowerment process model, likewise, self-efficacy drives the rest of the components: power-oriented goals, knowledge, competence, action, and impact. To measure whether the tool improves survivors’ abilities to achieve their housing goals, we have constructed a 10-item Housing Self-Efficacy Likert scale (Table 3), adapted from three existing scales to incorporate housing: the Generalized Self-Efficacy Scale [34], the Financial Self-Efficacy Scale [35], and the Scale of Economic Self-Efficacy [36]. The questions have been constructed using 4 response categories, from 1=strongly disagree to 4=strongly agree. Participants will be asked to rate their level of agreement on questions such as “I can always manage to solve difficult housing problems if I try hard enough” and “If I experience housing trouble, I can usually think of a solution.” To balance the potential “forced-choice” nature of the four categories, a “does not apply” option has also been added.

**Table 3 table3:** Housing self-efficacy scale.

No.	Item
1	I can always manage to solve difficult housing problems if I try hard enough.
2	If I have a housing problem, I can find ways to get what I need.
3	It is easy for me to stick to and accomplish my housing goals.
4	I am confident that I could deal efficiently with unexpected housing events.
5	Thanks to my resourcefulness, I know how to handle unforeseen housing situations.
6	I can solve most housing problems if I invest the necessary effort.
7	I can remain calm when facing housing difficulties because I can rely on my abilities.
8	When I am confronted with a housing problem, I can usually find several solutions.
9	If I experience housing trouble, I can usually think of a solution.
10	No matter what housing problem comes my way, I am usually able to handle it.

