9	My case manager has my best interest at heart.
10	My case manager makes me feel like I am worthy of their time.

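### The 75% instrument-feasibility rule uses a whole-survey denominator, so its verdict is not the response rate of any one outcome measure

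*Protocol article*

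**What the plan says.** Research question 4 asks: "Are the study’s processes and instruments feasible for a full-scale intervention trial". The section Large-Scale Trial Feasibility takes the response rate on the surveys as its proxy for instrument feasibility. That rate "will be calculated as the number of items answered on a survey divided by the total number of survey questions". The decision rule is "If a 75% response rate or higher is achieved, then the instrument will be deemed feasible". A does-not-apply "answer will count as an item nonresponse, or unanswered". The same section provides for a list of answered and unanswered questions, to help improve the instruments.

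The surveys hold three primary-outcome measures: a "10-item Housing Knowledge Quiz developed for this study", a "10-item Housing Self-Efficacy Likert scale", and the Staff Trust Scale, whose tenth and last item is "My case manager makes me feel like I am worthy of their time". Other questions differ by survey. On the baseline survey, "The study will collect sociodemographic information from participants at baseline", with seven variables named. The SC+ follow-up adds five usability items, two intent-to-use statements each with an open-ended follow-on, and questions on outcome appropriateness.

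Feasibility Criteria uses a survey-level count again: modification trigger (1) fires when at least 75% of the questions are unanswered.

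**The concern.** The verdict is worded for the instrument, but the rate belongs to the survey. A pooled rate averages over three primary outcomes and whatever else the questionnaire carries. A badly answered scale can be lifted over 75% by the rest, and a well answered one can be dragged below it.

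Nonresponse could well cluster here. The does-not-apply option is offered on the self-efficacy, trust and usability scales and counts as unanswered, while Table 2 shows no such option for the quiz. The Procedures section also allows that a participant may have no case-manager meeting during enrolment, and the trust scale asks about the case manager and those meetings. At stake is whether the study answers research question 4 for the scales that measure its primary outcomes. The full-scale sample size is to be estimated from those same three variables.

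**Working it through.** The article gives no calculation behind the 75% rule, so there is no figure to reproduce. The check applies the rule as written.

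**Inputs**
- Three scales of 10 items each (Tables 2 to 4).
- Pass at 75% answered.
- Survey length N is not stated. I use N = 30 for the three scales alone (assumed SC follow-up). I use N = 37 for 30 + 7 sociodemographic questions, assuming one question per named variable, or for 30 + 5 usability + 2 intent items. The SC+ follow-up is longer still once its open-ended questions are counted.

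**Fewest items of one 10-item scale compatible with a pass, all other items answered**

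Answers needed = 0.75 × N, rounded up. Minimum from the scale = answers needed − (N − 10), not below 0.

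| N | Needed | Other items | Minimum from the scale | Rate |
|---|---|---|---|---|
| 30 | 23 | 20 | 3 of 10 | 23/30 = 76.7% |
| 37 | 28 | 27 | 1 of 10 | 28/37 = 75.7% |
| 39 | 30 | 29 | 1 of 10 | 30/39 = 76.9% |
| 40 | 30 | 30 | 0 of 10 | 30/40 = 75.0% |

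**Other items answered at 90%**

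Break-even = 0.75 × N − 0.90 × (N − 10).
- N = 30: 22.5 − 18.0 = 4.5 of 10.
- N = 37: 27.75 − 24.3 = 3.45, about 3.5 of 10.

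**Reverse case, N = 30**

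Quiz 10/10 and both Likert scales 6/10: (10 + 6 + 6)/30 = 22/30 = 73.3%. The rule fails although the quiz was answered in full.

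**Same scale answers on different surveys**

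Take the SC follow-up at N = 30 and the SC+ follow-up at N = 37, where seven tool items are added.
- 27 of 30 scale items answered: SC 27/30 = 90%, pass. SC+ with the seven tool items unanswered: 27/37 = 73.0%, fail.
- 22 of 30 scale items answered: SC 22/30 = 73.3%, fail. SC+ with the seven tool items answered: (22 + 7)/37 = 29/37 = 78.4%, pass.

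**Per-scale denominator, same 75% cut**

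7/10 = 70% fails and 8/10 = 80% passes, whatever the survey length.

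**Trigger (1) against the 75% rule, N = 30**

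The trigger needs at least 23 unanswered (0.75 × 30 = 22.5, rounded up), so at most 7 answered. The feasibility rule needs at least 23 answered. A survey with 8 to 22 answers is therefore not feasible under one section and needs no modification under the other. The same gap appears at scale level: 3 of 10 answered is 70% unanswered, which does not reach the trigger.

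**The case against.** The strongest reply is that the instrument means the whole questionnaire. The formula is then self-consistent, and the plural in research question 4 could refer to the two surveys. This reading is open. It still leaves the study without a verdict on any of the three scales that carry its primary outcomes.

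Second, the list of answered and unanswered questions is finer than a per-scale rate and would expose a poorly answered scale. That stands: a reader might infer that the nonresponse would go unseen, and the article does not support that. But the list does not enter the 75% rule, so the label can contradict it.

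Third, the examples are extreme and the survey lengths assumed. That stands too, which is why the 90% case is shown.

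Fourth, a condensed article may leave tabulation detail to a fuller plan. Here, however, it fixes the numerator, the denominator, the handling of does-not-apply and the threshold, so the definition is stated rather than omitted.

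Two stronger readings should be resisted. One is that the SC+ follow-up is easier to pass because it has more questions. That holds only if the extra items are answered, and the 27/37 case shows the reverse. The other is that this rate selects which measures enter the full-scale trial or decides Stop or Go. The article gives it no such role: neither Stop criterion uses it, and Feasibility Criteria says the Go criteria concern enrolment and engagement.

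**Conclusion.** The point holds as a fault in how the rule is defined. As written, the 75% verdict is not the response rate of any one measure. With all other items answered, it can pass a primary-outcome scale with 3 of 10 items answered at N = 30 or 1 of 10 at N = 37. With other items at 90%, break-even is about 4.5 or 3.5 of 10. It can also fail a survey in which one scale is complete, and the same answers on one scale can meet different verdicts on different surveys, in either direction. The exact minima rest on assumed survey lengths, and clustering of nonresponse is plausible but not shown. The consequence is limited to the feasibility label and, because Feasibility Criteria also counts at survey level, to modification trigger (1).

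**What to change.** In Large-Scale Trial Feasibility, define the response rate for each instrument at each time point: items of that instrument answered, divided by its number of items times the number of returned surveys. Apply the 75% rule to each instrument and report the whole-survey rate as descriptive only.

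In Feasibility Criteria, restate modification trigger (1) on the same per-instrument rates. Reconcile its threshold (75% or more unanswered) with the feasibility rule (75% or more answered), so that an instrument failing the rule triggers a modification. Moving the per-instrument rates into the trigger without changing the threshold would not be enough, because a scale at 3 of 10 would still escape it.

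The cost is a sentence or two of definition and a few more rows of tabulation from item data already held in REDCap, with no added burden on participants. The small downside is that an instrument may be flagged that the pooled rate would have passed.

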#### Acceptability and Usability of the Tool

To understand the survivors’ and staff’s experiences of using the tool, we will collect data from the survivors through surveys (Table 5) and the staff through interviews (Textbox 1).

**Table 5 table5:** Perceived Usability Scale.

	Items
1	The tool is easy to use.
2	I had no trouble seeing the information in the tool.
3	The information in the tool is easy to understand.
4	The information in the tool is relevant to me.
5	I found the tool hard to use.

The survivors’ and staff’s intent to continue use and perceived effect will serve as proxies of the tool’s acceptability. In the follow-up survey to the SC+ group of survivors, intent to continue use will be measured by participants’ responses to the statements, “I plan to continue using the tool,” and “I would recommend the tool to others in a similar situation as me,” based on their tool use from the prior 2 weeks. For each statement, participants will also have an opportunity to elaborate on their answer with the open-ended question “Why?” Similarly, in the key informant interviews, staff will be presented with open-ended questions: “How likely are you to continue using the tool or recommend the tool to other case managers beyond the feasibility study? Why or why not?” To gauge the perceived effect, staff will be encouraged to identify changes in their workloads, relationships with survivors, and the survivors’ housing search approach after using the tool with questions like, “How does using the tool impact your or your staff’s workload? Do you have examples?” and “Have you noticed changes in your relationship with survivors as a result of using the tool?”

Perceived usability, on the other hand, will be measured through 5 items in the SC+ follow-up survey to survivors, as well as open-ended interview questions to the staff on navigation and content relevance. The 5-item measure to survivors was adapted from a 16-item Likert scale used to evaluate the bMORESafeapp [25] and has a response set ranging from 1=strongly disagree to 4=strongly agree, with a “does not apply” category for additional scenarios. Only five items of the original 16-item Likert scale measured general app usability. The remaining 11 items were specific to features found only in the bMORESafeapp.

Finally, the staff will be asked for their input on the future dissemination of the tool within the partner site and to other agencies through open-ended questions, like “How could the tool be used by others (eg, housing specialists, case managers, social workers, lawyers, real estate brokers, and other domestic violence advocates)?”

Key informant interview guide (outcome and questions).
**Introduction**
Tell me about yourself.How long have you worked at the partner site?What is your role at the site? What does that entail?What are you most proud of in your work?
**Intent to continue use (acceptability)**
How likely are you to continue using the tool with clients beyond the feasibility study? Why or why not? Scale of 1-4, 1=strongly disagree, 4=strongly agree.How likely are you to recommend the tool to other case managers beyond the feasibility study? Why or why not? Scale of 1-4, 1=strongly disagree, 4=strongly agree.

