### Study Population

The partner site, a community-based domestic violence program based in New York City, provides domestic violence and sexual assault counseling, case management, legal services, occupational therapy, and support groups for any survivor of domestic violence and is particularly attuned to the needs of survivors who are D/deaf or Hard of Hearing or have a disability [30]. Based on the last set of data collected by the site in 2021, the partner site, on average, served 171 new and existing clients per month. About 26% (n=45) of clients were new to the program each month. Of those who disclosed their information to the site, 84% (109/130) identified as a cisgender woman, and 15% (19/130) as a cisgender man. The majority identified as either Black (48/114, 42%) or Latino/a/x (32/114, 28%). None chose to disclose their employment status, but more than half (76/151) reported being on some form of public assistance. Finally, 52% (66/128) of clients reported a mental health disability, 18% (23/128) reported a sensory disability (ie, blindness or deafness), 17% (22/128) a physical disability, 10% (13/128) a medical condition, and 3% (4/128) a cognitive disability. The site has three full-time case managers, who cover a wide range of survivor needs including housing, and a full-time program director and assistant director who oversee the case managers.

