### Feasibility Criteria

As recommended by Thabane et al [44], we established formal Stop or Go criteria to evaluate the success of the feasibility study. A Stop outcome states that the subsequent large-scale trial is not feasible, while a Go outcome means that the study can continue, with or without modifications [44]. The outcomes will be determined after assessing the study data. We will stop if (1) no positive change approaching significance in any of the primary outcomes in SC+: survivors’ housing knowledge, housing self-efficacy, or staff trust, relative to SC, is observed; or (2) survivors, on average, do not intend to continue the use of the tool, as measured by scores of 2=Disagree or 1=Strongly Disagree on the Likert scale. Criteria #1 and #2 will help us determine whether SC+ shows promise of a positive effect and acceptability (as determined by intent to use) to warrant a subsequent intervention trial to a larger group. If either Stop criterion is met, then the full-scale study is not feasible.

If both Stop criteria are not met, then we can move to a Go, that is, continue to a large-scale trial. Modifications will be needed if (1) 75% or more of the questions in the survey are left unanswered, (2) 75% or more of potential survivor participants do not join the study, or (3) less than 95% of enrolled survivors do not complete both the baseline and follow-up surveys. This retention rate is informed by the retention rates of the web-based myPlan evaluation, which hovered around 94% at 6 months and 93% at 12 months [27]. The Go criteria will help us determine whether the study could enroll and engage sizable participation, as illustrated by the rates of recruitment, retention, and response. 

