### Statistical Analysis

Multiple linear regression models will be used to test the difference-in-difference in means of housing knowledge, housing self-efficacy, and staff trust. The inclusion of independent variables in the models will be determined by prior tests assessing whether any significant differences exist in outcome variables by demographic and moderating variables. The outcomes of interest will also be input as independent variables to determine the association between housing knowledge, housing self-efficacy, and staff trust.

Sample size, the rates of recruitment, retention, and response, and timeline will be recorded. Ease of implementation and outcome appropriateness will be collected through open-ended questions in individual interviews with the key informants, while acceptability and perceived usability will be collected through a mix of Likert scale and open-ended questions in the surveys and interviews.

To analyze the qualitative data, the written answers from the participant surveys and the transcripts from the key informant interviews will be inductively coded using a constant comparative method. Two coders will separately code the transcripts and then compare and iterate for agreement. Interrater reliability will be calculated as the number of codes in agreement, in proportion to the total number of codes [45]. We will iterate our codes until we achieve a minimum 80% agreement on 95% of our code set [45].

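### Both staff intent-to-continue-use items ask 'How likely' but are scored on a disagree-to-agree scale, and the body text describes the same question as open-ended: a minor instrument flaw to correct before the interviews

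*Protocol article*

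**What the plan says.** The key informant interview guide, under Intent to continue use (acceptability), contains two items. The first is "How likely are you to continue using the tool with clients beyond the feasibility study? Why or why not? Scale of 1-4, 1=strongly disagree"; the scale ends at 4 for strong agreement. The second is "How likely are you to recommend the tool to other case managers beyond the feasibility study? Why or why not? Scale of 1-4, 1=strongly disagree", with the same upper end. They are the only items in the staff guide that carry a numeric scale.

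The section Acceptability and Usability of the Tool gives these items their role. For survivors and staff alike, "intent to continue use and perceived effect will serve as proxies of the tool", and the sentence goes on to name acceptability as what they stand for. Survivors receive statements, the first being "I plan to continue using the tool". For the staff, the same section says that "staff will be presented with open-ended questions". It then prints one question that combines continuing use with recommending the tool, and it mentions no rating.

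The Statistical Analysis section says that "acceptability and perceived usability will be collected through a mix of Likert scale and open-ended questions in the surveys and interviews".

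On who will answer, Study Population lists three case managers and "a full-time program director and assistant director who oversee the case managers". Study Design and Eligibility Criteria both give five informants.

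**The concern.** An agreement scale needs a statement. Asked how likely they are to do something, an informant cannot strictly answer that they disagree. One person may treat 1 as very unlikely. Another may treat it as disagreement with something the interviewer has implied. The number is then recorded without a fixed meaning.

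At stake is the staff half of research question 5, which asks whether survivors and staff find the tool acceptable. Study Design describes the staff as people who can influence whether the tool stays in use after the study, so their stated intent is worth measuring cleanly.

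Two smaller matters belong to the same edit. The article disagrees with itself on whether staff give a rating at all. The first item also asks about the informant's own use with clients, although some informants supervise others who do that work.

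**Working it through.** The point concerns item wording, so the check is a comparison of passages and a few counts.

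**1. Stem against anchors**

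| Item | Form of the stem | Response scale | Do they fit? |
|---|---|---|---|
| Staff, continue use (interview guide) | Question on likelihood | 1-4, disagree to agree | No |
| Staff, recommend (interview guide) | Question on likelihood | 1-4, disagree to agree | No |
| Survivor, continue use (Acceptability and Usability) | Statement | Agreement, as the labels in Feasibility Criteria show | Yes |
| Survivor, recommend (same section) | Statement | Not printed beside the item; taken to be the same | Yes |

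The article thus holds a well-formed version of both items, but only for survivors.

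**2. Is a staff rating planned?**

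- Acceptability and Usability of the Tool: open-ended, no scale, one combined question.
- Interview guide: two separate items, each with a 1-4 scale and a request for reasons.
- Statistical Analysis: a mix of Likert and open-ended questions across surveys and interviews.

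The second and third agree. The first differs from the guide in both the scale and the number of questions.

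**3. Number of ratings affected**

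- Informants: 3 case managers + 1 program director + 1 assistant director = 5. This reproduces the stated five.
- Scaled ratings: 2 items × 5 informants = 10, all with the mismatch.
- Weight of one informant on one item: 1/5 = 20%.
- Informants who are directors: 2/5 = 40%, assuming that the five are the staff listed in Study Population. This bears on the first item only.

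**4. Decisions affected**

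Feasibility Criteria holds two Stop rules and three rules for modification, 2 + 3 = 5. The only one that uses intent is met when "survivors, on average, do not intend to continue the use of the tool, as measured by scores of 2=Disagree or 1=Strongly Disagree", which rests on survivors alone. The others rest on the change in the primary outcomes, unanswered survey questions, survivors not joining, and completion of both surveys. Staff ratings enter 0 of 5. The Statistical Analysis section plans no comparison of staff with survivor scores.

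**5. Wording for supervisors**

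Under Perceived effect, the guide words the questions on workload and on changed relationships so that they cover the informant or the staff. The intent item on use with clients has no such alternative.

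**The case against.** A reader might infer that the staff ratings cannot be read as intent at all. The documents do not support that. The items stand under a heading that names intent, 1 is plainly the negative end and 4 the positive end, and each item asks for reasons. They are put live in individual interviews of 60 minutes, where an interviewer can clarify. The scores are loosely anchored, not unreadable.

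A reader might also infer that a comparison of staff with survivors is spoiled. No such comparison is planned.

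Nor does the staff half of research question 5 hang on these two numbers. Perceived effect is a second staff proxy with its own questions, and with five informants the evidence is mainly qualitative. All of this stands, and it limits the size of the point. It does not make the stem fit the scale.

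On directors, it would go too far to say that the first item does not suit two of the five. Study Population says that they oversee the case managers; it does not say that they never use the tool with clients. Study Design expects all five informants to talk about their experience with the tool. Other questions in the guide also refer to the informant's own clients or meetings without mentioning staff, and the guide opens by asking each person's role. What remains is a reasonable precaution in wording.

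**Conclusion.** The mismatch is real and stands in the printed guide: both scaled staff items pair a likelihood question with agreement anchors, so all 10 planned ratings are ambiguous. The body text and the guide also disagree on whether the staff question carries a rating.

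The effect is minor. It is confined to a descriptive result on staff acceptability from five people. No Stop or Go decision, planned comparison or primary outcome depends on it.

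The count of two directors assumes that the informants are the five staff listed in Study Population. That a director may not use the tool with clients personally is an inference, and it concerns the first item only.

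**What to change.** Edit the guide before the interviews, which Results places in June 2024, in one of two ways:

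- **Statements with the present scale.** Build the first item on the survivors' statement, "I plan to continue using the tool", adding 'with clients', and make the second a statement that the informant would recommend the tool to fellow case managers. Keep the 1-4 agreement anchors and the request for reasons.
- **Likelihood questions with a matching scale.** Keep 'How likely' and anchor 1-4 from very unlikely to very likely, again with the request for reasons.

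The first option also brings the staff items into line with the survivors' items.

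In either case, word the first item to cover 'you or your staff', as the guide already does under Perceived effect. Amend Acceptability and Usability of the Tool so that it describes two items, each with a rating and an open-ended follow-up, in agreement with the guide and with Statistical Analysis.

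Report the five ratings together. A separate row for directors would hold two people, identifiable by their posts at one site, and would add no statistical information.

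The cost is two edited lines in the guide and one sentence in the body text. No extra participants, data or interview time are needed. If any interviews have already been held with the present wording, report those ratings with the mismatch stated and read them together with the reasons given.
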